**Protocol S3. The study protocol approved by ethics committee – English version**

**SUMMARY OF THE STUDY PROTOCOL, ETHICAL COMMITTEE**

**BACKGROUND OF THE STUDY**

Hypertension is one of the most important national health concerns and approximately half of the middle-aged adults in Finland have high blood pressure (Antikainen et al. 2006). Hypertension increases the risk for cardiovascular events.

Cold temperature causes an immediate rise in blood pressure among all people. In addition, blood pressure remains at a higher level during the cold season (Brennan et al. 1982, Mitchell et al. 2002, Modesti et al. 2006, Sun 2010). Global studies have shown an inverse relation between temperature, as well as high seasonal variation in blood pressure (Alpérovitch et al. 2009, Barnett et al. 2005). An elevated blood pressure is an important determinant of the cold-related morbidity and mortality. However, blood pressure responses to cold exposure among hypertensive subjects are not yet well-known. Experimental studies have shown that blood pressure medication results in lower blood pressure level during cold exposure among subjects with mild hypertension (Komulainen 2007).

**AIM OF THE STUDY**

The aim of the study is to assess blood pressure responses among (untreated) hypertensive people during cold exposure similar to everyday winter circumstances. Responses will be compared to blood pressure changes among healthy individuals.

The specific goals are:

1. to assess the magnitude and timing of blood pressure increase during cold exposure and to compare the responses between hypertensive and healthy subjects.
2. to assess the timing of blood pressure recovery after the cold exposure.
3. to assess the effect of cooling of different parts of the body to blood pressure.
4. to assess the factors affecting blood pressure changes (e.g. blood coagulation factors).

**SIGNIFICANCE OF THE STUDY**

The study provides novel knowledge on blood pressure dynamics during cold exposure among hypertensive people. This knowledge is useful for healthcare professionals for advising hypertensive patients for proper cold protection or for medical doctors considering medication for their hypertensive patients. The knowledge provided by the study can be applied to reduce or prevent cold-related health events among hypertensive patients, such as myocardial infarctions and strokes.

**MATERIAL AND METHODS**

**MATERIAL**

The study subjects are men with untreated high blood pressure or healthy men. They are 55-65 years old residents of the city of Oulu, Finland.

**Recruitment**

A random sample is drawn from the Finnish Population Register Centre from residents of Oulu (55-65 years old men). Subjects are contacted by phone and a short interview is applied to evaluate the eligibility of the subjects. People with diagnosed/treated high blood pressure, coronary artery disease (CAD) or respiratory disease are excluded because the study aims for examining persons with untreated hypertension and excluding other cold-related health risk factors. Eligible men are asked for consent to perform blood pressure measurements. Subjects measure their blood pressure at home according to national guidelines: two measurements in the morning and evening daily for one week. According to the mean value of those 28 measurements, the subjects are classified either to patient (≥ 140/90 mmHg, high untreated blood pressure) or control (≥ 130/85 mmHg, normal blood pressure) group.

The subjects with high normal blood pressure in home measurements (≥ 130/85 mmHg) are advised to contact their health care center or health care professionals, who will carry out the diagnosis and initiate treatment for high blood pressure. These subjects are simultaneously encouraged to attend to the experimental study. The subjects with blood pressure ≥ 180/110 mmHg are advised to contact emergency care and they are excluded from the study.

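### The control group is defined by home blood pressure at or above 130/85 mmHg, which shuts out normotensive men, contains the patient group and carries two conflicting labels

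*Protocol*

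**What the plan says.** The protocol's Recruitment section classifies each man on the average of a week of home readings: "According to the mean value of those 28 measurements, the subjects are classified either to patient" or control. The two limits stand in one sentence: "patient (≥ 140/90 mmHg, high untreated blood pressure) or control (≥ 130/85 mmHg, normal blood pressure) group".

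The following paragraph of the same section uses the identical cut-off with another label: "The subjects with high normal blood pressure in home measurements (≥ 130/85 mmHg) are advised to contact their health care center" for diagnosis and treatment. These men are also encouraged to take part in the experiment. The upper end is closed: "The subjects with blood pressure ≥ 180/110 mmHg are advised to contact emergency care and they are excluded from the study".

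Elsewhere the comparison group is described in words. The aims state: "Responses will be compared to blood pressure changes among healthy individuals". The Material section states: "The study subjects are men with untreated high blood pressure or healthy men". The Sample size section plans hypertensive and normotensive men in a 2:1 ratio, 60 and 30. None of these sections gives a different numerical limit for controls.

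**The concern.** One cut-off with one direction cannot describe both normal pressure and high normal pressure. It also cannot be the rule for a healthy comparison group if the same men are being sent for diagnosis and treatment.

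This sentence is the only operational definition of the comparison group. Specific goal 1 compares the rise in blood pressure during cold between hypertensive and healthy men, so group membership is the contrast under study. If the rule is followed as printed, the men whom the aim calls healthy are not recruited as controls, and the control role falls to men just under the hypertensive limit. If staff instead follow the label and ignore the symbol, the limit is whatever each of them takes it to be.

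**Working it through.** **Inputs.** All are from the protocol's Recruitment section unless noted.
- Classification basis: 2 readings × 2 times a day × 7 days = 28, which agrees with the stated 28.
- Patient: ≥ 140/90. Control: ≥ 130/85. Excluded: ≥ 180/110.
- Planned groups: 60 + 30 = 90 (Sample size section).
- Systolic SD: 21 mmHg (Sample size section).

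**Step 1. Apply the printed rule to example home means.** The protocol does not say whether a limit such as 140/90 needs both components or either one, so each case is tried both ways, with the same convention for both limits.

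| Home mean | Patient / control, both components needed | Patient / control, either component suffices |
|---|---|---|
| 120/80 | no / no | no / no |
| 129/84 | no / no | no / no |
| 130/85 | no / yes | no / yes |
| 135/87 | no / yes | no / yes |
| 139/89 | no / yes | no / yes |
| 140/90 | yes / yes | yes / yes |
| 150/95 | yes / yes | yes / yes |
| 179/109 | yes / yes | yes / yes |

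Three results hold under either convention:
1. A man below 130/85 on both components is in no group.
2. Since 140 > 130 and 90 > 85, every man who meets the patient limit meets the control limit, so the two classes are not exclusive.
3. If patients are removed first, the overlap goes, but the controls that remain are only men who reach 130/85 and not 140/90.

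**Step 2. Set the labels side by side.** At or above 130/85 is normal in the classification sentence and high normal in the referral sentence. The aims, the Material section and the Sample size section require healthy or normotensive men. Result 3 contradicts all three.

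**Step 3. Reverse the sign as a test.** With controls below 130/85, the 120/80 and 129/84 men become controls and the overlap disappears. The 130/85, 135/87 and 139/89 men are then in neither group, although they are encouraged to attend and the plan of 60 + 30 has no third group.

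**Step 4. Sample size.** The plan's formula is n = 2 × SD² / difference² × f = 2 × 21² / 20² × 10.5 = 23.15, against the stated 23 per group. It reproduces and does not depend on the control cut-off.

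**Step 5. Illustration of the resting contrast.** Assume that home systolic pressure is normal with SD 21 and a mean of 130, 135, 140 or 145 mmHg. The protocol gives no mean, and diastolic pressure is ignored. Shares are normal probabilities, and group means are truncated-normal means.

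| Assumed mean | Share < 130 | Share 130-139 | Mean < 130 | Mean 130-139 | Mean 140-179 | Gap, controls < 130 | Gap, controls 130-139 |
|---|---|---|---|---|---|---|---|
| 130 | 50% | 18% | 113.2 | 134.9 | 152.7 | 39.4 | 17.8 |
| 135 | 41% | 19% | 114.9 | 135.0 | 153.7 | 38.8 | 18.7 |
| 140 | 32% | 18% | 116.4 | 135.1 | 154.9 | 38.5 | 19.8 |
| 145 | 24% | 17% | 117.7 | 135.2 | 156.1 | 38.4 | 20.9 |

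The gap is in resting pressure. It is not the outcome of goal 1.

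**The case against.** **It is a one-character slip.** The labels normal, healthy and normotensive make the intent plain, and the document is an English version, so a typing or translation error is likely. A fault in reading the PDF cannot be fully excluded either, although the same symbol appears in all four cut-offs of the section and makes sense in the other three. The harm arises only if staff apply the symbol against its label. This stands as an account of how the error came about. It does not make the error harmless, because no other sentence gives the control limit. Correcting the sign also leaves the men between the limits without a group.

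**The figures in millimetres are weak.** This stands. The SD of 21 is not shown to apply to means of 28 home readings after diagnosed or treated men are excluded. With an assumed SD of 12 to 15, the gap against controls below 130 is about 26 to 31 mmHg. The assumed means put 32 to 59% of men at or above 140, whereas the protocol's own prevalence figures (17% untreated, about 33% treated and so excluded) suggest about 0.17 / 0.67 = 25%, hence a mean near 126. The ratio of roughly one half is less sensitive than the gaps themselves.

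**A reader might infer that the cold-response difference is biased toward zero.** The documents do not support this. It would require the response to rise steadily with resting pressure. No section says so, and the background says that responses in hypertensive people are not yet well known.

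**A reader might infer that the referral sentence concerns only borderline men.** Its printed range has no upper limit below 180/110, so it also covers the eligible patients, and encouraging them to attend is how that group is recruited. Only the men between the two limits lack a group.

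**A reader might infer that an isolated systolic elevation can be assigned freely.** Under the printed rule, a man at 145/80 is in neither group if both components are needed and in both groups if either suffices. The convention may also be set in an analysis plan or operating document that is not at hand.

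**Conclusion.** The point holds as an error in the definition of the comparison group. As printed, the rule excludes from the control group every man below 130/85 on both components. It places the patient range inside the control range, and it contradicts the protocol's own description of the controls in the aims, the Material section and the Sample size section. This follows from the text alone. The overlap assumes that the same component convention applies to both limits, and it disappears if patients are classified first. The exclusion of men below 130/85 and the conflict of labels remain in every case.

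The consequence for the results cannot be sized from the documents. A resting systolic gap of about 18 to 21 mmHg instead of 38 to 39 is an illustration that rests on assumed means, an SD of 21 and no use of diastolic pressure. Neither the direction nor the size of any bias in the cold-response comparison can be derived. The sample size calculation is not affected. Because the sentence decides who is compared with whom, it needs correction before screening.

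**What to change.** In the Recruitment section, reconcile the classification and referral sentences:

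1. Reverse the control inequality so that it agrees with the protocol's own label of normal pressure and no longer overlaps the patient criterion.
2. State which group, if any, men between the two cut-offs (130-139/85-89) belong to, and whether they count toward the planned 60 + 30. Once the sign is reversed they are encouraged to attend but fit neither group.
3. While editing, it would help to say whether both components or either one must meet each limit. This is a request for clarity, and the documents do not dictate the answer.

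A separate intermediate group that does not count toward 90 is one possible answer to item 2. The documents do not require it. The referral advice and the upper exclusion limit are not part of this change.

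The cost is a sentence or two before screening, with no added subjects or procedures and no change to the sample size.

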**Sample size**

Assumptions for sample size estimation: Variation of blood pressure among the study subjects (men, aged 55-65 years, residents of Oulu) is 21/11 mmHg (FINRISK 2002-basic report). An average increase in blood pressure during -5⁰C cold exposure is 20/20 mmHg (Komulainen 2007).

90 % power was aimed and 0.05 was chosen for type I error bound. This resulted to function f (a,b) value of 10.5 and sample size ((2 x (21 mmHg)2) / (20 mmHg)2) x 10.5 = 23 subjects / group. Each group should consist of minimum of 30 subjects to have sufficient amount of data for the analyses. A 2:1 ratio of hypertensive and normotensive subjects is aimed, which results into patient group of 60 subjects and total amount of 90 subjects.

The prevalence of hypertension is ca. 50% among 25-64 years old men in Finland and ca. 1/3 of them are untreated (Kastarinen et al. 2009), i.e. prevalence of untreated hypertension is ca. 17% among adult Finnish men. Sample size for screening of the subjects from the Finnish Population Register Centre is 0.17 x N = 60 → N = 353 subjects. To consider the loss of follow-up, a sample of 500 men will be applied.

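### The 90% power is calculated from the average cold rise and the spread of blood pressure level, so it has no basis for the hypertensive-versus-healthy comparison of responses in goal 1

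*Protocol*

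**What the plan says.** The first goal under Aim of the study has two parts: "to assess the magnitude and timing of blood pressure increase during cold exposure and to compare the responses between hypertensive and healthy subjects". The first part concerns the rise itself, the second a contrast between two groups.

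The Sample size section of the protocol takes two inputs. The spread is "Variation of blood pressure among the study subjects (men, aged 55-65 years, residents of Oulu) is 21/11 mmHg (FINRISK 2002-basic report"). The effect is given as "An average increase in blood pressure during -5⁰C cold exposure is 20/20 mmHg". The error rates are stated as "90 % power was aimed and 0.05 was chosen for type I error bound", followed by "This resulted to function f (a,b) value of 10.5" and then "sample size ((2 x (21 mmHg)2) / (20 mmHg)2) x 10.5 = 23 subjects / group".

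The section then raises the number: "Each group should consist of minimum of 30 subjects to have sufficient amount of data for the analyses". With a 2:1 ratio this becomes 60 hypertensive and 30 normotensive men. It does not say which comparison the 90% refers to. The protocol nowhere gives an expected difference in response between the groups or an SD of the response.

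**The concern.** The formula 2σ²/δ² × f is the standard one for comparing two independent means. Applied to goal 1's comparison of responses, δ has to be the difference between the two groups' mean rises, and σ the between-subject SD of the rise. The protocol instead enters the average rise as δ and the spread of blood pressure level as σ. Each is a legitimate quantity, but neither is the one that the group comparison needs.

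This is the only power statement in the protocol, and a reader will naturally attach it to the central comparison. If that comparison then proved non-significant, the claimed 90% would encourage the conclusion that hypertensive men respond as healthy men do. The Significance section intends the results to inform advice on cold protection and decisions on medication, so such a misreading would matter.

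**Working it through.** **1. The protocol's own figure.** For two-sided 0.05 and 90% power, f = (1.960 + 1.282)² = 10.51, which matches the stated 10.5. Then 2 × 21² / 20² × 10.5 = 2 × 441 / 400 × 10.5 = 23.15, stated as 23 (24 if rounded up). The figure reproduces, so the fault is not in the arithmetic.

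**2. Read as a difference in rise between groups.** A δ of 20 mmHg would mean that one group's rise exceeds the other's by the whole average cold effect, for example 40 versus 20 or 20 versus 0 mmHg. Nothing in the protocol suggests that such a difference is expected.

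**3. Read as warm versus cold.** The variance of a within-person change is 2σ²(1 − ρ), where ρ is the correlation of the warm and cold readings. At ρ = 0 it equals 2σ², and n = 2σ²f/δ² is the number of men needed in each group to show a 20 mmHg rise, treating the two readings as independent. Any positive correlation lowers the requirement. At ρ = 0.5 the SD of change is 21 mmHg and n = 441/400 × 10.5 = 11.6, so 12 men by the normal approximation (14 by the t distribution). Groups of 30 and 60 are ample for this, but it concerns only whether there is a rise.

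**4. What 60 + 30 gives for the group comparison.** The SD of the rise must be assumed. With a level SD of 21 mmHg, SD of change = 21 × √(2(1 − ρ)), which is 9.4 at ρ = 0.9, 16.3 at ρ = 0.7 and 21 at ρ = 0.5. I therefore use 10, 15 and 21 mmHg.

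- Standard error of the difference: SD × √(1/60 + 1/30) = 0.2236 × SD.
- Detectable difference at 90% power: by the normal approximation 3.2415 × 0.2236 = 0.725 × SD; by the non-central t with 88 degrees of freedom 0.733 × SD.
- Power: non-central t with 88 degrees of freedom and non-centrality difference / (0.2236 × SD). For example, 10 / (0.2236 × 15) = 2.98 gives 84%.

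| Assumed SD of rise (mmHg) | Detectable at 90% power (mmHg) | Power for 10 mmHg | Power for 5 mmHg |
|---|---|---|---|
| 10 | 7.3 | 99% | 60% |
| 15 | 11.0 | 84% | 31% |
| 21 | 15.4 | 56% | 18% |

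The 10 and 5 mmHg targets are illustrations, a half and a quarter of the 20 mmHg rise. The protocol names no target.

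**The case against.** The strongest reply is that the protocol never says the 90% belongs to the group comparison. Measuring the rise is also part of goal 1, and with warm and cold readings treated as independent, 20 and 21 mmHg are the right kinds of input. On that reading the result is a conservative number per group. This stands. A reader might infer that the calculation powers a hypothesis the study does not test, but the text does not support that. What remains is that the powered comparison is not named and no calculation covers the group contrast.

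A reader might also infer that the design cannot see a clinically relevant difference. That is not supported either. The protocol gives no clinically relevant difference and no SD of the rise, and at an SD of 10 mmHg a 10 mmHg difference has 99% power. The figure of 21 mmHg may also be pessimistic as the basis for these SDs: the groups are formed by cutting on blood pressure and the highest values are excluded, so the spread of level within each group could be smaller. On the other hand, a warm–cold correlation below 0.5 with a level SD of 21 mmHg would put the SD of the rise above 21.

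Finally, details of analysis and reporting may sit in a statistical analysis plan that is not shown. That does not answer the point, because the protocol itself makes the power claim and fixes its inputs.

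**Conclusion.** The point holds in a limited form. The 23 per group is computed correctly, but on either reading the stated 90% is not supported for comparing the cold response between hypertensive and healthy men. It would apply either to a group difference as large as the entire average rise, or to the existence of the rise, for which the sample is ample.

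For the group comparison, 60 + 30 men can detect 0.73 × SD of the rise with 90% power. That is about 7 to 15 mmHg over assumed SDs of 10 to 21 mmHg. Whether this is adequate depends on an SD and a target difference that the protocol does not state, so the finding concerns the justification and not the sample size itself.

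**What to change.** Keep 60 + 30 and rewrite the power paragraph in the Sample size section:

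- Say that the 20 mmHg calculation concerns the rise itself, with warm and cold readings treated as independent.
- For the group comparison, define the target as the difference between groups in mean systolic change (cold minus warm) and state the detectable difference at 90% power, two-sided 0.05, as 0.73 × SD of change.
- Take that SD from the pilot measurements scheduled for spring 2011 if they include the cold exposure. The protocol does not say whether they do. Otherwise give the range: 7.3 / 11.0 / 15.4 mmHg for SDs of 10 / 15 / 21 mmHg, with the powers for 10 and 5 mmHg tabulated above.

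This costs one paragraph and no extra subjects. The downside is that the stated power becomes less favourable.

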**METHODS**

**Questionnaire**

The study subjects fill in a questionnaire to assess for factors possibly affecting blood pressure, such as occupation, health status, smoking, alcohol consumption, diet, physical activity, mental condition, and cold sensation (questionnaire attached).

**Cold exposure**

The study subjects are prepared with skin temperature sensors and a blood sample is drawn before cold exposure. Also, central blood pressure, arterial stiffness and blood pressure in warm environment are measured. Measurement excitement is minimized by introduction and habituation to the experimental conditions before the measurements. During the experiment a 15 minutes whole body cold exposure with winter clothing is implementedin controlled circumstances in a climatic chamber with air temperature of -15ºC and wind of 2m/s. The subjects stand still during the exposure. The subjects are followed in warm conditions after the cold exposure.

**Parameters to be measured**

1. Blood pressure (ambulatory measurements before, during, and after cold exposure)
2. Central blood pressure and arterial stiffness (pulse wave velocity)
3. Skin temperature: 6 measurement points (limbs, body)
4. Blood sample before cold exposure. Health related parameters will be analyzed from blood sample, such as red and white blood cells, coagulation factors, and blood lipids. We might perform genetic analyses to evaluate relation of cold temperature and high blood pressure.
5. Thermal sensations and comfort, cold related symptoms (during cold exposure)
6. Body composition with bio-impedance measurement (InBody)
7. Aerobic fitness: physical fitness measurements while resting (Polar Own Index)

**IMPLEMENTATION AND SCHEDULE OF THE STUDY**

The recruitment of the study subjects and pilot measurements are performed during spring 2011. The experimental measurements are implemented from August to September 2011. Collected data will be analyzed in 2012 and 2013.

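### The patient group is defined as untreated, yet the plan refers these men for treatment months before the cold exposure and states no rule for those who have started it

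*Protocol*

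**What the plan says.** **Who is studied.** Under Material: "The study subjects are men with untreated high blood pressure or healthy men". Aim of the study likewise names untreated hypertensive people, to be compared with healthy men.

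**Screening.** Under Recruitment, men are interviewed by phone. Those with diagnosed or treated high blood pressure, coronary artery disease or respiratory disease "are excluded because the study aims for examining persons with untreated hypertension and excluding other cold-related health risk factors".

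**Grouping.** One week of home readings follows. "According to the mean value of those 28 measurements, the subjects are classified either to patient" (mean at or above 140/90 mmHg) or control.

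**Referral.** In the same section, men at or above 130/85 mmHg are advised to see clinicians "who will carry out the diagnosis and initiate treatment for high blood pressure. These subjects are simultaneously encouraged to attend to the experimental study".

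**Timing.** The section on implementation and schedule states: "The recruitment of the study subjects and pilot measurements are performed during spring 2011. The experimental measurements are implemented from August to September 2011".

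**Relevance of treatment.** The Background reports that "blood pressure medication results in lower blood pressure level during cold exposure among subjects with mild hypertension".

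**What is collected besides.** The Questionnaire section covers health status among other topics and refers to an attached form that is not shown. The Cold exposure section includes a blood pressure reading in warm conditions before the exposure.

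**The concern.** The plan excludes treated men at the phone interview and then advises the men it has just classified as hypertensive to go where treatment begins. It tests them later under the same label. Nothing stated says what happens to a man who has started medication by the time he enters the chamber: whether he is still eligible, which group he belongs to, or how his data are used.

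At stake is the meaning of the patient group. If part of it is treated at the time of measurement, its results no longer describe untreated hypertension, which is the study's declared subject. On the protocol's own account of medication, blood pressure levels during exposure would then be lower than in the intended population. A larger sample does not remove such a shift.

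**Working it through.** **The sections side by side**

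1. Material and Aim of the study require untreated hypertension. Recruitment gives this requirement as the reason for excluding treated men.
2. A man in the patient class (at or above 140/90) is also at or above 130/85, so the whole patient group receives the referral advice.
3. The advice leads to professionals "who will carry out the diagnosis and initiate treatment for high blood pressure", and the same men are encouraged to attend the experiment.
4. The home week is not dated, but it is described under Recruitment, which the schedule puts in spring. If spring means March to May (an assumption), the gap to the experiment runs from about two months (end of May to start of August) to about seven (start of March to end of September). That leaves time to start treatment.
5. The phone interview is the only stated point at which treatment decides eligibility. The pre-exposure reading and the health-status questions are not tied to eligibility or group.

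Followed as written, the sequence can therefore place treated men in the untreated group.

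**Size of the shift.** Let p be the share of the 60 patients who have started treatment and t the mean change that treatment makes in the quantity measured. The patient mean moves by p × t, that is 0.2t, 0.3t or 0.5t at p = 20%, 30% or 50%. The protocol gives neither p nor t, so no figure in mmHg can be stated.

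**The plan's own sample size.** Inputs from Sample size: SD 21 mmHg, difference 20 mmHg, multiplier 10.5. Then 2 × 21² / 20² × 10.5 = 23.15, which reproduces the stated 23 per group. The planned groups are 60 and 30.

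**Cost of keeping only untreated men.** With equal SDs in the two groups, the standard error of the group difference is proportional to √(1/n₁ + 1/n₂). Relative to 60 versus 30, the ratio is √(1/(60(1−p)) + 1/30) / √(1/60 + 1/30), and the denominator is √0.05.

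| Assumed p | Untreated men left | SE ratio | Classified men needed to keep 60 untreated, 60/(1−p) |
|---|---|---|---|
| 20% | 48 | √(0.05417/0.05) = 1.04 | 75 |
| 30% | 42 | √(0.05714/0.05) = 1.07 | 86 |
| 50% | 30 | √(0.06667/0.05) = 1.15 | 120 |

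With the plan's 20 and 21 mmHg and two-sided α of 0.05, power is 98.9% at 60 versus 30. After restriction it is 98.4%, 97.9% and 95.8% at the three values of p. These power figures only illustrate: the 20 mmHg is described as the average rise in the cold, not as a difference between groups.

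**The case against.** The strongest reply has five parts.

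- **A check may exist.** The document is headed a summary and the attached questionnaire is not shown. It may ask about medication, and blood pressure is read before exposure. This stands: a reader might infer that treatment status is never checked again, and the text does not prove that. What remains is that no stated rule ties either source to eligibility, group or analysis.
- **Contamination need not be confined to patients.** A reader might infer that only the patient group is affected. The control class is printed as at or above 130/85 mmHg, the same threshold that triggers referral, so read literally the controls are referred too. If that sign is a misprint, the effect falls on patients, but the document does not settle it.
- **Bias in aim 1 is not shown.** Aim 1 compares the magnitude and timing of the increase, whereas the Background sentence concerns the level under medication. A reader might infer that the group difference in the rise is diluted. The documents give neither an effect on the rise nor its direction.
- **Season.** The Background says that "blood pressure remains at a higher level during the cold season", and a reader might infer that a spring classification is wrong by late summer. A seasonal change in level can act on both groups and does not make the spring class an error.
- **Analysis plan.** How treated men enter the analysis could be left to a statistical analysis plan. That is partly fair. But the definition of the study population and the recording of medication at the visit belong in the protocol, and a later plan cannot reliably recover what was not collected.

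The referral is also only advice, so uptake may be small. That limits the size of the problem but does not remove the contradiction.

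**Conclusion.** The point holds in a limited form. The protocol defines its patient group as untreated, directs that group towards treatment, tests it months later, and states no rule for men who have started. The group can therefore include treated men, and levels during exposure in that group could be biased.

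The documents do not support saying that the group will be treated to any particular extent, or that the comparison of rises in aim 1 is biased in a known direction. The standard-error increases of 4%, 7% and 15% measure the cost of the remedy at assumed uptakes; they do not measure the bias. The conclusion rests on placing the home week in spring with the rest of recruitment, and on no rule being hidden in the attachment.

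This is a should-fix point, held with moderate confidence.

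**What to change.** - Reconcile Material, Recruitment and Implementation and schedule of the study, so that the definition of the patient group, the referral and the timing of the experiment agree. No view is taken here on whether or when treatment should start.
- Record current antihypertensive medication and its start date at the chamber visit, whether or not the questionnaire already asks.
- Define the patient group for aim 1 as men still untreated on the day of exposure, and report men who have started treatment separately. The interview criterion covers diagnosed as well as treated hypertension, so state which of the two applies on that day.

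The cost is a short item at the visit, a sentence or two in the protocol, and a somewhat smaller patient group, with the loss of precision tabulated above. Keeping 60 untreated men would instead mean classifying more men, for example 86 at an assumed 30%.

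Repeating the home week before the visit is optional. It would update the blood pressure class, but it adds a further week of readings per man, and the documents do not show it to be necessary.
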